### Sirolimus (rapamycin) administration

Participants assigned to the intervention group will receive sirolimus (rapamycin) at a dose of 6 mg per week, administered orally in the form of three capsules containing an unaltered 2 mg tablet of sirolimus (rapamycin) each. To measure treatment and dose adherence, the rapamycin will be blister-packed. Both used and unused blister packs must be returned to the site and collected at the 6-week and 13-week intervals for investigational product reconciliation.

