## Participant timeline {13}

### Schedule of assessments

**Table Tabe:** 

Procedures and assessments	Visit 1	Visit 2	Visit 2a	Visit 3	Visit 4
	Screening	Baseline	Phone call	Interim assessment	EOS
	Day -28 to -1	Day 0	Within 6 days of baseline	Day 42±7	Day 91 +7
Informed consent	x				
Review of subject eligibility	x	x			
Demographics^1^	x				
Medical history	x				
Auscultate the heart to check for murmurs	x				
Vital signs^2^	x	x		x	x
ECG	x				
Hematology and biochemistry	x^3^			x^4^	x^3^
DNA methylation (TruDiagnostics)		x			x
SF-36 questionnaire		x			x
Assessment of ability to complete 30-Second Chair-Stand Test	x				
Randomization		x			
Allocation of weekly medication^5^		x		x	
Confirm participant day 1			x		
Weekly participant contact			x^6^		
Adverse event collection		x	x	x	x
Distribute subject diary card		x		x	
Collect subject diary cards				x	x
30-Second Chair-Stand Test		x		x	x
Hand grip strength		x		x	x
6-min walk test		x			x

^1^Race, gender at birth, contact details, height, and weight

^2^Resting heart rate, blood pressure, and oxygen saturation

^3^Full blood count, eGFR, urea and electrolytes, LFTs, HbA1c, lipids, IGF-1, hs-CRP

^4^Full blood count, LFTs, lipids

^5^Allocation of investigational product for 6-week period, followed by a 7-week period

^6^Participants are to be contacted by phone each week. Participants who cannot be reached following two phone contact attempts in a week can be sent a text message or email

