### Participant activities schedule

Weeks 1–13 exercise and dosing schedule.

Day 1 Week 1 must begin within 6 days of Day 0 (baseline visit).

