**Table Tabf:** 

**Weekly schedule**	**Exercise schedule**	**Dosing schedule**
Day 1	Training program	No treatment
Day 2	Rest day	No treatment
Day 3	Training program	No treatment
Day 4	Rest	No treatment
Day 5	Training program	No treatment
Day 6	Rest day	Placebo/rapamycin in the morning
Day 7	Rest day	No treatment

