### Participant diary

At baseline (visit 2) and visit 3, participants will be provided with a printed diary to complete daily. Information to be recorded will be the date, study required exercise program completed or any deviation from the assigned exercise program, other exercise completed that day not required by the protocol, study medication administration, and recording of any adverse event that has prevented the participant from completing the assigned exercise program or the assigned rapamycin dosing schedule.

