### Statistical methods

#### Statistical methods for primary and secondary outcomes {20a}

As some of the feasibility issues are related to the efficacy analyses, they are described first. The efficacy analysis plan is intended to match the analysis plan of the full trial closely.

Efficacy analysisAnalysis sets◦ Intention-to-treat (ITT) analysis set: This set will be used for the primary analysis and will include all randomized participants in their originally assigned groups.◦ Per-protocol (PP) analysis set: this set will be used for sensitivity analyses and will include participants who complete at least 75% of the exercise sessions and take at least 75% of the protocol-stipulated doses of sirolimus (rapamycin) or placebo.General inferential analysis plan◦ Outcomes at 13 weeks will be analyzed using regression models, adjusting for baseline values of the outcomes. Generalized linear models (GLM) will be employed, selected during a blind review of the data without knowledge of group allocation.◦ Final analyses will utilize the selected GLMs, and parametric assumptions will be addressed using the wild bootstrap method to estimate standard errors [35, 36]. For larger trials, standard sandwich estimators of the variance would be used in lieu of the bootstrap.Handling missing data◦ Multiple imputations will be used to create 15 completed datasets. The nominal significance level for this phase 2a study will be set at 0.1; however, in line with current thinking regarding preliminary studies, the results will deemphasize testing and emphasize point and interval estimation, producing confidence intervals for active arm effect having between 75% and 95% confidence levels in increments of 5 percentage points [27].Sensitivity analyses◦ Sensitivity analyses will be performed on the per-protocol analysis set and the complete-data-only set, excluding cases with missing data.

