Safety analysisSafety analysis set: this set includes all randomized participants. Adverse events will be allocated on an as-treated basis:◦ Events occurring before cessation of treatment or completion of the trial will be assigned to the randomized arm.◦ Events occurring after cessation will be assigned to the placebo arm.Analysis of adverse events:◦ Counts of adverse events will be regressed on the allocation arm as described above in interaction with the graded severity using negative binomial regression.◦ Dichotomized relatedness to the intervention (classified as possible, probable, or definite) will be regressed on the allocation arm using a quasi-binomial framework with logarithmic link (relative risk regression) or a relative risk working model (e.g., Poisson with bootstrap estimation of the variance) to test for non-inferiority of the rapamycin arm. Standard errors will be estimated using the bootstrap, resampling participants. The modalities of non-inferiority will be detailed in the final analysis plan.

Feasibility analysesScreening and randomization rates: overall and weekly screening and randomization rates will be reported with Poisson-based 95% confidence intervals.Cessation and withdrawal rates: rates of drug treatment cessation, exercise program cessation, and study withdrawal will be reported and compared across randomization arms using a log-rank test.Residual variance estimation: the residual variance of each outcome will be estimated to inform the sample size and analytical design of the phase 3 trial.

Adherence to medicationAdherence reporting: adherence to the medication will be reported by arm at 6 and 13 weeks using mean percentage of supply used and compared between arms using binomial regression with bootstrap-based standard errors and *p*-values [30].Causal effect estimation: the causal effect of the medication on the primary outcome will be estimated using two-stage residual inclusion estimation, with the randomized allocation as the instrumental variable [31].

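### Medication adherence is scored on doses supplied rather than doses due, so a participant who misses nothing can score 83% at week 6, and the shortfall can carry into week 13

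*Protocol article*

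**What the plan says.** Under Adherence to medication in Statistical methods {20a}, the protocol article says that "adherence to the medication will be reported by arm at 6 and 13 weeks using mean percentage of supply used", and that the arms are then compared by binomial regression. The schedule behind that measure is spread over several sections:

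- **Supply.** Footnote 5 to the Schedule of assessments reads "Allocation of investigational product for 6-week period, followed by a 7-week period". The number of doses per pack is not given.
- **Return of packs.** Sirolimus (rapamycin) administration says: "Both used and unused blister packs must be returned to the site and collected at the 6-week and 13-week intervals".
- **Visits.** In the Schedule of assessments, baseline is Day 0, Visit 3 is Day 42±7 and Visit 4 is Day 91 +7.
- **Start of dosing weeks.** The Participant activities schedule lets Week 1 Day 1 fall up to 6 days after Day 0. Visit 2a exists to "Confirm participant day 1".
- **Dose day.** The weekly table puts "Placebo/rapamycin in the morning" on Day 6 of each participant week.

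The per-protocol set uses a different basis. Participants must "take at least 75% of the protocol-stipulated doses of sirolimus (rapamycin) or placebo".

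**The concern.** A percentage of supply counts any supplied dose not used by pack return as non-adherence, including a dose that was not yet due. The article names both parts of the ratio and nowhere adjusts the denominator for doses still to come.

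A lag before Week 1 is plausible. Under Provision of exercycle, the supplier is contacted only after randomization and then arranges delivery with each participant.

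What is at stake is the accuracy of a reported result in a study that Sample size {14} calls a feasibility study. Full adherence at week 6 could be published as something lower, with the gap and part of the spread set by appointment dates.

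**Working it through.** The article gives no adherence figure to reproduce, so the check is a count over the calendar.

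**Inputs.** Week 1 Day 1 falls on study day s = 1 to 6. Dosing is on Day 6 of each week. Visit 3 is on Days 35 to 49 and Visit 4 on Days 91 to 98. Six doses in the first supply and seven in the second are assumptions, read from the 6-week and 7-week periods with once-weekly dosing. A dose due on the visit morning counts as taken.

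**Dose dates.** Dose k is due on study day s + 5 + 7(k − 1).

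- Dose 5: s + 33, Days 34 to 39
- Dose 6: s + 40, Days 41 to 46
- Dose 13: s + 89, Days 90 to 95

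**Visit 3 exactly on Day 42, counted from Day 0.** Dose 6 is due by then only if s + 40 ≤ 42, that is s = 1 or 2. For s = 3 to 6 a fully adherent participant scores 5/6 = 83.3%. If a share p starts on Day 3 or later, the mean under full adherence is 100% − 16.7p: 95.8% at p = 25%, 91.7% at 50% and 83.3% at 100%.

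**All permitted dates.** Score = min(6, doses due) / 6.

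| Visits counted from | Cases | 100% | 83% | 67% |
|---|---|---|---|---|
| Day 0, starts on Days 1–6 | 90 date pairs | 39 | 41 | 10 |
| Day 0, adding same-day starts (s = 0) | 105 date pairs | 49 | 46 | 10 |
| Day 0, visits on Days 39–45 only | 42 date pairs | 15 | 27 | 0 |
| Participant Day 1 | 15 days | 9 | 6 | 0 |

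These count date combinations. They are not frequencies, because the article gives no distribution of starts or visits. The ten 67% pairs are s = 3 with Day 35, s = 4 with Days 35–36, s = 5 with Days 35–37 and s = 6 with Days 35–38. On the participant-Day-1 count, dose 6 falls on Day 41, so visits on Days 35 to 40 score 83%. If a dose due on the visit day is not counted, the 90 pairs split 33, 42 and 15, and 7 of the 15 participant-count days score 83%.

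**Late Visit 3.** In three pairs (s = 1 with Day 48 or 49, s = 2 with Day 49) a seventh dose is already due, although only six were supplied.

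**Week 13, taken as cumulative over 13 doses.** The result depends on what happens to unused doses at Visit 3.

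- *Kept by the site, seven more issued.* After five used, at most 5 + 7 = 12, or 12/13 = 92%. After four used, at most 4 + 7 = 11, or 11/13 = 85%. The date of Visit 4 does not change this. On the participant-Day-1 count, visits on Days 35 to 40 carry the 12/13 limit.
- *Handed back to the participant.* The only shortfall is a Visit 4 before dose 13. Counted from Day 0, this gives 12/13 in 10 of 48 pairs. Counted from participant Day 1, dose 13 is on Day 90 and there is none.

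**The case against.** The strongest objection is that this is derivation detail. A journal article condenses a fuller protocol, and how a not-yet-due dose is handled normally belongs in the analysis plan. That would stand had the article left the measure open. It fixes the measure as percentage of supply used, and following that text gives the scores above.

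Two objections stand in part. Which day visits are counted from is not beyond dispute. Counting from Day 0 is the plainer reading of the schedule, but on the participant count an on-time visit scores 100% and the 67% cases vanish. The pack size is also unstated, although any overage would enlarge the denominator and lower the score further.

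The consequence is small, and this stands in full. No threshold or go/no-go rule rests on week-6 adherence, and the data collected allow the figure to be restated later.

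Several stronger readings are tempting but unsupported:

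- *A 67% score would drop adherent participants from the per-protocol set.* It would not, because that set counts protocol-stipulated doses. Even 11 of 13 (85%) clears 75%.
- *The comparison between arms is biased.* Start dates and visit dates should be alike in randomized, blinded arms, so added noise is expected but bias is not.
- *The two dose bases contradict each other.* A pack summary and an analysis-set criterion may differ.
- *The planned causal-effect estimate is distorted.* The article does not say which exposure measure enters it.

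A more reassuring reading, that a late Visit 4 repairs week 13, holds only if unused doses are handed back. The article says that they are collected and does not mention re-issue.

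**Conclusion.** The point holds and is minor. As written, the week-6 measure can score full adherence at 83%, through the start lag alone at a visit on Day 42 (visits counted from Day 0) or through the visit window alone. It falls to 67% only for some early visits counted from Day 0. At week 13 the ceiling can be 92% or 85% if unused doses stay with the site. The level of a reported feasibility result is understated by an amount that depends on unknown dates. It is zero at week 6 if everyone starts on Days 1–2 and attends on Day 42.

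The conclusion assumes one supply unit per weekly dose, six then seven doses issued, and a cumulative week-13 figure.

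**What to change.** In the adherence paragraph of Statistical methods {20a}, replace percentage of supply used with the following, for both the 6-week and the 7-week period: doses taken, divided by doses that fell due between dispensing and pack return while supply was in hand, capped at the doses supplied. Doses taken are the blister count checked against the dated diary, which records "study medication administration". Doses due follow from participant Day 1 as confirmed at Visit 2a.

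A fully adherent participant then scores 100% in each period. The cap covers the three late-visit pairs, which would otherwise score 6/7 = 86%. It also covers a second period in which more than seven doses fall due against seven supplied.

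The change is a short rewording that uses dates, counts and diary entries already collected. Visits, packs and dispensing stay as they are. The cost is slightly more derivation work.

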## Interim analyses {21b}

No interim analyses are planned for this study and is based on several considerations:Study design and duration: the study is a relatively short-term phase 2a trial with a 13-week intervention period. Given the limited duration, the benefits of conducting interim analyses are minimal compared to the additional complexity and potential risks of unblinding or bias.Safety monitoring: continuous safety monitoring will be in place throughout the trial. Adverse events will be closely monitored and reviewed by the study team and an independent safety monitor to ensure participant safety without the need for formal interim analyses.Efficacy evaluation: the primary and secondary outcomes will be assessed comprehensively at the end of the study. Conducting interim analyses will not provide sufficient additional information to justify potential disruptions or modifications to the trial.

Continuous monitoring of participant safety will be maintained, with any serious adverse events or safety concerns being reported to the sponsor, ethics committee, and regulatory authorities as required.

### Methods for additional analyses (e.g., subgroup analyses) {20b}

Subgroup analyses: subgroup analyses will be conducted to explore the potential differential effects of the intervention across various participant characteristics and to provide a more detailed understanding of the efficacy and safety of sirolimus (rapamycin) in conjunction with exercise. These additional analyses are not limited to the following:Age groups: participants will be stratified into age groups (65–74 and 75–85 years) to assess whether the intervention’s effectiveness varies with age.Gender: the impact of the intervention will be evaluated separately for male and female participants to identify any gender-specific effects.Baseline fitness levels: participants will be grouped based on their baseline fitness levels, as measured by the 30-Second Chair-Stand Test (30CST) and other baseline assessments, to determine if initial fitness influences the intervention’s outcomes.Adherence to protocol: Subgroup analyses will consider adherence levels, comparing outcomes between participants who adhered strictly to the exercise and medication regimen (≥75% adherence) and those with lower adherence.

Adjusted analyses: adjusted analyses will be performed to account for potential confounding factors and to provide a more accurate estimate of the intervention's effects.Baseline covariates: the primary and secondary outcome analyses will be adjusted for relevant baseline covariates, such as age, gender, baseline fitness levels, and any other significant factors identified during the blind review of the data.Generalized linear models (GLM): these models will be used to account for repeated measures and the correlation between baseline and follow-up assessments.

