## Sample size {14}

The sample size was selected primarily to satisfy logistic constraints of this feasibility study. As this study is not confirmatory, we do not predicate the sample size primarily on power considerations: arm sizes of 20, assuming no withdrawals, will provide 80% and 90% power, respectively, to detect fairly large Cohen’s effect sizes of 0.8 and 0.9, respectively, at a nominal significance level of 0.1.

In regard to safety, the arm sizes and post-randomization follow-up time will enable to detect rate ratios of adverse events between the sirolimus (rapamycin) and placebo arms varying between 2.4 and 3.7, dependent upon the rate in the placebo arm and the dispersion of the data. Sample sizes of 12 per arm have been indicated as sufficient for pilot or feasibility studies [34]. However, our feasibility objective of variance estimation makes it preferable to aim for a total sample size of 40, as a 95% confidence interval for the variance will then have expected half-width of less than half the true variance, providing a reasonably precise estimate.

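### Evaluating men and women separately does not estimate the sex difference the plan wants to identify; an arm-by-sex interaction with its interval would

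*Protocol article*

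**What the plan says.** The protocol's section on additional analyses {20b} gives the general aim: "subgroup analyses will be conducted to explore the potential differential effects of the intervention across various participant characteristics". For gender it then names both a method and a purpose: "the impact of the intervention will be evaluated separately for male and female participants to identify any gender-specific effects".

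Gender appears once more in that section, as an adjustment variable: "the primary and secondary outcome analyses will be adjusted for relevant baseline covariates, such as age, gender, baseline fitness levels". That gives gender a main effect and no arm-by-gender term. The only interaction in an analysis model is in the safety analysis {20a}, where adverse event counts are regressed on arm "in interaction with the graded severity using negative binomial regression".

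On inference, {20a} says that "The nominal significance level for this phase 2a study will be set at 0.1". The same sentence says that testing will be played down in favour of point and interval estimates, with intervals from 75% to 95%.

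**The concern.** An effect specific to one sex means that the treatment effect in men differs from the treatment effect in women. The quantity to estimate is that difference. Separate evaluations give two estimates, each with its own interval, and leave the reader to compare them by eye. Two intervals may overlap while the interval for the difference excludes zero. One may exclude zero and the other include it while the difference is close to nothing. Neither pattern answers the question asked.

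Small subgroups make the comparison fragile. The trial has 20 per arm, so each sex contributes perhaps 10 per arm, and randomisation is stratified by age only, so the arms need not balance within each sex. What is at stake is a misread exploratory result. {20a} also says that the efficacy plan is meant to match that of the full trial closely, so the wording could carry forward.

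**Working it through.** **Inputs from the protocol.** 20 per arm, 1:1 allocation and no withdrawals (Trial design {8}, Sample size {14}); nominal level 0.1; effect sizes d = 0.8 and 0.9 ({14}). **Assumed:** the sex split, which the protocol does not give; and a two-sided test, since sidedness is not stated.

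**1. Reproduce the plan's own figure.** {14} states that "arm sizes of 20, assuming no withdrawals, will provide 80% and 90% power, respectively", for "effect sizes of 0.8 and 0.9, respectively, at a nominal significance level of 0.1". Two-sided at 0.1 with 20 per arm, the normal approximation gives 81.2% at d = 0.8 and 88.5% at d = 0.9. The noncentral t gives 79.9% and 87.5%. One-sided versions give 89% and 94%, which do not fit. Two-sided 0.1 is therefore used below.

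**2. Power within one sex.** With n per arm, the noncentrality is d × √(n/2) on 2n − 2 degrees of freedom. For n = 10 the critical value is 1.734 on 18 df.

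| n per arm | d | noncentrality | power |
|---|---|---|---|
| 10 | 0 | 0 | 10.0% |
| 10 | 0.5 | 1.118 | 28.8% |
| 10 | 0.8 | 1.789 | 53.1% |
| 14 | 0.8 | 2.117 | 66.1% |
| 6 | 0.8 | 1.386 | 36.4% |

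**3. Probability that exactly one sex is significant when the true effect is the same in both.** The formula is p₁(1 − p₂) + p₂(1 − p₁).

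- d = 0, 10/10 split: 2 × 0.100 × 0.900 = 18%
- d = 0.5, 10/10 split: 2 × 0.288 × 0.712 = 41%
- d = 0.8, 10/10 split: 2 × 0.531 × 0.469 = 50%
- d = 0.8, 14/6 split: 0.661 × 0.636 + 0.364 × 0.339 = 54%

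**4. The same situations with an interaction test.** The difference between the two sex-specific effects is tested in one pooled model at 0.1. Its false-positive rate is 10% by construction, whatever the common effect. Simulation (40,000 runs per case; 10/10 and 7/13 splits; d = 0, 0.5, 0.8 and 0.9) gave 9.6% to 10.1%.

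**5. What the interaction can detect.** In SD units the standard error of the difference at an equal split is √(2/10 + 2/10) = 0.632. On 36 df the critical value is 1.688, so a 90% interval has an expected half-width of about 1.688 × 0.632 = 1.07 SD. Power for a true difference of 0.8 SD (noncentrality 0.8/0.632 = 1.265) is about 35%. A difference of about 1.6 SD is needed for 80% power.

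**The case against.** The strongest objection is that the protocol never says how the two sex-specific results will be compared. It does not say that each sex will be tested at 0.1, or that significance in one sex only will count as a difference. It calls the study not confirmatory, calls the subgroup work exploratory, and puts intervals ahead of tests. Sex-specific estimates shown side by side fit that text. This stands: the discordance figures describe a rule that a reader might apply, not one to which the plan commits. A reader might infer that the plan will usually produce a false sex difference. The documents do not support that, and even under the rule, discordance is the minority outcome at d = 0 and d = 0.5.

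A second objection is that model detail for subgroups belongs in an analysis plan that is not shown. This stands only in part. The gender sentence names separate evaluation as the means and identifying sex-specific effects as the end. An analysis plan that followed it literally would still lack the contrast.

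A reader might extend the point to the age and baseline fitness subgroups. The wording does not support it. Age groups are formed "to assess whether the intervention’s effectiveness varies with age", which names no separate analysis and is already compatible with an interaction. The fitness item is worded in the same open way. A reader might also infer that a false sex effect would set eligibility or stratification in the next trial. The protocol does not say so; the input to phase 3 design that it names in {20a} is residual variance.

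Finally, the interaction has little power here. That is true. Its wide interval shows how little 40 participants can say about a sex difference, which two separate estimates leave hidden.

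**Conclusion.** The point holds for the gender sentence alone. As written, the method does not deliver the quantity that it is meant to identify: it yields no estimate and no interval for the difference in effect between men and women, and nothing else in the protocol supplies one. That conclusion needs no assumption about testing.

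The numerical risk is conditional. It requires reading a difference from significance at 0.1 in one sex only, the same true effect in both sexes, no withdrawals and an assumed sex split. Under those conditions the separate results disagree in 18% to 54% of trials over the cases in step 3, against about 10% for an interaction test. The analysis is exploratory, in a feasibility study that plays down testing, so this is a minor improvement and does not threaten the primary result.

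**What to change.** Replace the gender sentence in {20b} with:

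> Effect modification by sex will be estimated by an arm-by-sex interaction in the primary model, reported with its confidence interval; sex-specific estimates will be taken from that model and read as exploratory.

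The cost is one sentence and one extra model term, with no new data. It suits the plan's preference for estimation, because the difference gets its own interval. The drawback is imprecision, so the report should say that a non-significant interaction is not evidence of equal effects in men and women. The age and baseline fitness items need no change on this ground.

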**Methods:**

This randomized, double-blind, placebo-controlled trial will enroll 40 participants aged 65–85. Participants will be randomly assigned to receive either sirolimus (rapamycin) 6 mg/week or placebo for 13 weeks, in conjunction with an at-home exercise program. The primary outcome measure is the change in muscle strength and endurance, assessed by the 30-Second Chair-Stand Test. Secondary outcome measures include adverse events, changes in muscle strength and endurance as measured by the 6-min walk test, handgrip strength, and participant-reported outcomes using the SF-36 survey. Assessments will be conducted at baseline, mid-intervention (week 6), and post-intervention (week 13). Blood samples will be collected for hematology and biochemistry analyses, including full blood count, urea and electrolytes, liver function tests, HbA1c, lipids, serum IGF-1, and hs-CRP. DNA methylation will be analyzed using TruDiagnostic™ to explore changes in biological age.

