## Trial design {8}

This study is a randomized, double-blind, placebo-controlled trial designed to evaluate the effects of once-weekly sirolimus (rapamycin) 6 mg on muscle strength and endurance in older adults participating in a thrice-weekly exercise program for 13 weeks. Randomization will be carried out using block randomization with stratification for age with a 1:1 allocation to receive either once-weekly sirolimus (rapamycin) or a placebo in addition to their exercise regimen. The primary, exploratory objective is to evaluate whether this combined intervention is at least equivalent to regular exercise alone in enhancing muscle performance in older adults.

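### The baseline-fitness subgroup groups 40 participants on several measures; one continuous arm-by-baseline-30CST interaction would answer the same question with about a third less loss of information

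*Protocol article*

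**What the plan says.** Under Methods for additional analyses {20b}, the baseline-fitness item says that "participants will be grouped based on their baseline fitness levels, as measured by the 30-Second Chair-Stand Test (30CST) and other baseline assessments". Its stated purpose is to find out whether initial fitness influences the intervention's outcomes. The other assessments are not named. The schedule of assessments shows grip strength and the 6-min walk test at the baseline visit alongside the 30CST, so at least three measures are candidates. The same section introduces its list with the words "These additional analyses are not limited to the following".

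Under Statistical methods {20a}, "Outcomes at 13 weeks will be analyzed using regression models, adjusting for baseline values of the outcomes". Baseline 30CST is therefore already in the model for the 30CST outcome as a main effect. That section sets a nominal level of 0.1 for the study and states that estimates and intervals will be given more weight than tests. It assigns no level to subgroup analyses.

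On size, the abstract says "This randomized, double-blind, placebo-controlled trial will enroll 40 participants aged 65–85", and Sample size {14} states that "arm sizes of 20, assuming no withdrawals, will provide 80% and 90% power" for "effect sizes of 0.8 and 0.9, respectively, at a nominal significance level of 0.1".

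**The concern.** The question is one of effect modification by a quantity that is measured as a count and is already in the model. Grouping participants on it treats everyone within a group as equally fit and discards the differences among them. With 20 per arm there is little information on an interaction to begin with, so the loss matters. Allowing more than one measure also gives the same question several possible answers, with nothing in the protocol to say which one counts.

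What is at stake is modest. A real dependence of the sirolimus effect on starting fitness is more likely to be missed than it need be, and an apparent dependence on one of several measures is harder to interpret. The primary comparison and the safety analysis are untouched. Statistical methods {20a} does say that the efficacy plan is meant to match that of the full trial closely, so the choice could carry forward.

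**Working it through.** **Inputs from the protocol article:** 40 participants, 1:1 allocation, 20 per arm (Abstract; Trial design {8}; Sample size {14}); nominal level 0.1 (Sample size {14}; Statistical methods {20a}); baseline value of the outcome in the model (Statistical methods {20a}).

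**Assumptions, not in the documents:** normally distributed baseline measures; baseline-outcome correlation 0.6 in the control arm, so with outcome SD 1 the residual SD is √(1 − 0.6²) = 0.8; a linear interaction of 0.3 or 0.6 SD per baseline SD; correlation 0.5 between baseline measures.

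**1. The protocol's own power figures.** The noncentrality is d × √(20/2), on 38 degrees of freedom, two-sided 0.1.
- d = 0.8: 79.9% (t), 81.2% (normal); stated 80%.
- d = 0.9: 87.5% (t), 88.5% (normal); stated 90%.

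The stated figures are reproduced to within about 2.5 points, reading 0.1 as two-sided.

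**2. Size of the groups.** 40/2 = 20 per fitness group, hence about 10 per arm per group. Within one such group, power for d = 0.8 at 0.1 falls from about 80% to 53% (t) or 56% (normal). This is the power to see an effect inside one group, not to see a difference between groups.

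**3. Information lost by a median split.** For a normal variable and a linear interaction, the relative efficiency of a median split is 2/π = 0.637. The loss is 1 − 0.637 = 0.363, about 36%.

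**4. Power for the interaction, continuous term.** With n = 20 per arm and a random normal baseline of SD 1, the mean of 1/Sxx in each arm is 1/(20 − 3) = 1/17. So SE ≈ 0.8 × √(2/17) = 0.274. The two-sided 0.1 critical value on 36 degrees of freedom is 1.688.
- Slope 0.3: 0.3/0.274 = 1.09, power about 29%.
- Slope 0.6: 0.6/0.274 = 2.19, power about 69%.

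**5. Power for the interaction, median split.** Multiply the noncentrality by √0.637 = 0.798.
- Slope 0.3: 1.09 × 0.798 = 0.87, power about 22%.
- Slope 0.6: 2.19 × 0.798 = 1.74, power about 53%.

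**6. Simulation of the same set-up** (20 per arm, both analyses adjusted for baseline 30CST):

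| True slope (SD per baseline SD) | Median split | Continuous term |
|---|---|---|
| 0 (false-positive rate) | 0.10 | 0.10 |
| 0.3 | about 22% | about 28% (28% to 30% across runs) |
| 0.6 | about 53% | about 70% |

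The simulation and the approximation agree.

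**7. More than one measure.** If a median split on each of three baseline measures were tested at 0.1, independent tests would give 1 − 0.9³ = 0.27 for at least one false positive. Simulation gives about 0.25 (0.25 to 0.27 for correlations from 0.6 to 0). One continuous term on one named measure gives one test, at about 0.10.

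**The case against.** **The testing is inferred.** A reader might take every measure and every grouping to be a separate test at 0.1. The protocol does not say so. Statistical methods {20a} gives 0.1 as a nominal study level while moving the emphasis to estimation, and {20b} speaks of exploring differential effects. This stands, so the 0.25 is conditional on such tests being made.

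**Larger error rates can be constructed.** Searching three cut-points on the 30CST gives about 0.22, and the best of three cut-points on each of three measures gives about 0.48 to 0.49. The second figure needs nine looks with the best one picked. The protocol mentions neither a cut-point search nor thirds, and a cut-point is detail that an analysis plan, not shown here, commonly supplies. The same holds for closing the subgroup list. The exploratory label is largely there already: Sample size {14} calls the study not confirmatory. None of these carries the point.

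**The information loss can be overstated.** A reader might infer that grouping throws away most of the information. A median split keeps about 64% of it.

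**The power gain depends on the assumed slope.** A slope of 0.6 is large: it equals the assumed control-arm baseline slope. At smaller slopes both methods are weak: 13% against 15% at 0.15, 17% against 20% at 0.2, and 31% against 43% at 0.4 (split against continuous). This stands, and it is why a range is shown.

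**The gain also depends on linearity.** If the effect changes by a step at average fitness, the split does slightly better: 26% against 23% for a step of 0.6 SD, and 49% against 44% for 1.0 SD. This stands too. Grouping is not an error in itself; it is the less efficient choice when the change is gradual.

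**Conclusion.** The point holds as a low-cost improvement to an exploratory analysis. It is not a defect in the primary analysis. Grouping 40 participants on baseline fitness loses about 36% of the information on a roughly linear interaction, which costs about 6 power points at a slope of 0.3 SD per baseline SD (22% against 28%) and about 17 at 0.6 (53% against 70%). Using several measures could raise the chance of at least one false positive to about 0.25, but only if each of three were split and tested at 0.1, which the protocol does not state.

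These figures rest on normal baseline measures, a residual SD of 0.8, a linear interaction and no dropout. With 40 participants neither method reliably detects a moderate interaction. The gain is a more precise single estimate of effect modification, and it disappears if the true change is a step.

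**What to change.** In the baseline-fitness item of {20b}, for the 30CST outcome:
- Name baseline 30CST as the single fitness measure for this analysis.
- Replace the grouping with one arm-by-baseline-30CST interaction, baseline kept continuous, in the week-13 model. The interaction is what is needed, since the baseline main effect is already there.
- Report the interaction estimate with its interval, and the fitted sirolimus effect with intervals at a low, a middle and a high baseline score.

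This suits the protocol's preference for estimation over testing. The cost is a change of wording and one model term. The downsides are the assumption of an approximately linear change of effect with baseline score and the loss of a simple two-group table, for which the three fitted effects largely make up. The change deals with the fitness item only; the age, gender and adherence subgroups are not affected by it.
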